### Secondary end points

The secondary end points are the incidence of each of the Saranas EBBMS level 1, 2, and 3 indicators and the incidence of all BARC type III or V bleeding.

### Safety end points

The following end points will be analyzed, as applicable: access site-related bleeding complications; access site-related vascular complications; access site-related blood transfusions; non–access site-related bleeding complications; non–access site-related vascular complications; non–access site-related blood transfusions; all blood transfusions; hemoglobin drop; death; device and procedure-related adverse events; serious adverse events; and serious adverse device effects. All safety end points will be adjudicated per the BARC bleeding criteria (Table 2), the Valve Academic Research Consortium 3 (VARC-3)^15^ vascular and access-related complications definitions (Supplemental Appendix Table 1), and the VARC-3 bleeding and transfusions criteria (Supplemental Appendix Table 2).

### Health economics

In addition to the main clinical study, data from the SAFE-MCS study will be used to perform an economic analysis of the potential economic benefit of the Saranas EBBMS. Since the SAFE-MCS study lacks a concurrent control group, external data will be used to estimate the frequency and costs of bleeding complications in patients treated according to standard of care. Costs associated with bleeding and vascular complications of large-bore access will be estimated using data from either the Nationwide Inpatient Sample or National Readmission Database. Then, based on historical data, a decision-analytic model will be developed to estimate the cost offsets associated with the Saranas EBBMS.

To support the health economics effort of the study, each study site will perform a retrospective chart review of the 10 most recent complex high-risk PCI cases with Impella support without the use of the Saranas EBBMS (∼150 patients) that meet the inclusion and exclusion criteria for SAFE-MCS. These data will be used to estimate the frequency of specific bleeding and vascular complications in patients who underwent Impella-supported PCI without EBBMS monitoring prior to the start of the SAFE-MCS study. Resources utilization, cost, and outcomes will be compared between the 2 groups retrospectively.

Because historical data may overestimate the complication rate in contemporary practice, sensitivity analyses will be performed to examine the relationship between the expected rate of complications with standard practice and the projected cost savings with the Saranas EBBMS.

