### Primary end points

The primary end point is incidence of access-site related bleeding (Bleeding Academic Research Consortium [BARC]^14^ type III or V). For the principal analysis of the primary end point, bleeding events are adjudicated per the BARC bleeding criteria shown in Table 2.

**Table 2 tbl2:** BARC bleeding criteria.

**Type 0:** No bleeding
**Type 1:** Bleeding that is not actionable and does not cause the patient to seek unscheduled performance of studies, hospitalization, or treatment by a healthcare professional; may include episodes leading to self-discontinuation of medical therapy by the patient without consulting a healthcare professional
**Type 2:** Any overt, actionable sign of hemorrhage (eg, more bleeding than would be expected for a clinical circumstance, including bleeding found by imaging alone) that does not fit the criteria for type 3, 4, or 5 but does meet at least 1 of the following criteria: (1) requiring nonsurgical, medical intervention by a healthcare professional, (2) leading to hospitalization or increased level of care, or (3) prompting evaluation
**Type 3a:** Overt bleeding plus hemoglobin drop of 3 to 5 g/dL^a^ (provided hemoglobin drop is related to bleed); any transfusion with overt bleeding
**Type 3b:** Overt bleeding plus hemoglobin drop 5 g/dL^a^ (provided hemoglobin drop is related to bleed); cardiac tamponade; bleeding requiring surgical intervention for control (excluding dental/nasal/skin/hemorrhoid); bleeding requiring intravenous vasoactive agents;
**Type 3c:** Intracranial hemorrhage (does not include microbleeds or hemorrhagic transformation, does include intraspinal); subcategories confirmed by autopsy or imaging or lumbar puncture; intraocular bleed compromising vision
**Type 4:** CABG-related bleeding; perioperative intracranial bleeding within 48 h; reoperation after closure of sternotomy for the purpose of controlling bleeding; transfusion of 5 U whole blood or packed red blood cells within a 48-h period^b^; chest tube output 2L within a 24-h period
**Type 5a:** Probable fatal bleeding; no autopsy or imaging confirmation but clinically suspicious
**Type 5b**: Definite fatal bleeding; overt bleeding or autopsy or imaging confirmation

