## Statistical considerations

### Sample size calculations and assumptions

The primary efficacy aim of this study is to demonstrate the incidence rate of access site-related BARC type III or V bleeding is reduced compared with the historical incidence rate. The secondary efficacy aims are to estimate the incidence rate of activation of each of the EBBMS level 1, 2, and 3 indicators and the incidence rate of all BARC type III or V bleeding and to investigate whether there is an association between the level of indicator and BARC type. The safety aim is to estimate the overall complication/adverse event rate as well as the adverse event rates related to the EBBMS.

The PROTECT II study enrolled 216 patients undergoing nonemergent high-risk PCI under MCS with Impella support.^16^ Investigators reported a major bleeding rate (defined as BARC III or V bleeding) of 12.5%. In the SAFE-MCS study, a 50% reduction in access-site bleeding rate (P) under surveillance with the EBBMS is estimated. The magnitude of reduction was chosen based on what was perceived to be clinically meaningful by the medical trial leadership and took into account that not all bleeding events are access-related and could be reduced by the use of the Saranas EBBMS. Assuming that the rate of bleeding (P) is 6.25%, a sample size of 184 evaluable subjects is required to achieve 90% power for a 1-sample exact binomial test at the 1-sided 0.05 alpha level.

Data will be summarized by sample size (N), mean, standard deviation, minimum, median, and maximum for continuous variables and by sample size and frequency and percentage of discrete variables. For all subjects included in this study, demographics (age, sex, race/ethnicity), medical history, physical examination, and laboratory tests will be summarized.

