### Analysis of primary efficacy end points

The incidence of access-related BARC type III or V bleeding events will be defined dichotomously as bleed or no bleed. The frequency and proportion of subjects with a primary efficacy end point will be calculated along with the upper 95% confidence bound. Success will be based on showing the confidence bound is less than the historical rate of 12.5%

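### Bleeding is to be called reduced against a fixed historical 12.5% that is not checked for the primary claim, although recent same-site control cases are already being collected

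*Protocol article*

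**What the plan says.** Under Sample size calculations and assumptions, the primary efficacy aim "is to demonstrate the incidence rate of access site-related BARC type III or V bleeding is reduced compared with the historical incidence rate". The historical rate comes from one source: "The PROTECT II study enrolled 216 patients undergoing nonemergent high-risk PCI under MCS with Impella support", and "Investigators reported a major bleeding rate (defined as BARC III or V bleeding) of 12.5" percent. The trial is sized at 184 evaluable subjects for 90% power with a one-sample exact binomial test at one-sided 0.05, assuming 6.25% with the device.

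Under Analysis of primary efficacy end points, the decision rule is "Success will be based on showing the confidence bound is less than the historical rate of 12.5" percent. No other reference rate enters the primary analysis.

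The Health economics section takes a more cautious view of historical rates: "Because historical data may overestimate the complication rate in contemporary practice, sensitivity analyses will be performed". What those analyses vary is the expected complication rate under standard practice, and what they examine is projected cost savings. The same section has each site review its 10 most recent Impella-supported high-risk PCI cases done without the monitor, about 150 in all, which must meet the SAFE-MCS eligibility criteria. Of these it says "These data will be used to estimate the frequency of specific bleeding and vascular complications in patients who underwent Impella-supported PCI without EBBMS monitoring". It also plans a retrospective comparison of resource use, cost and outcomes between the two groups.

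The Limitations section names the single-arm design but does not discuss whether the historical rate might be too high.

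**The concern.** The plan admits a weakness in historical rates where they feed the cost model, and says nothing of it where a historical rate alone decides the primary result. If Impella-supported PCI without the monitor now bleeds less than 12.5%, some or all of a primary success could reflect better general practice, yet the aim as worded would report it as a reduction. The study is already gathering the evidence most relevant to this: recent cases without the device, from the same sites, under the same eligibility criteria. The article gives that evidence no part in the primary conclusion.

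**Working it through.** **Inputs.** Null rate 12.5%, from 216 patients; assumed rate with the device 6.25%; n = 184; one-sided alpha 0.05 (all from the two statistical sections). About 150 chart-review cases (Health economics). The rates of 11%, 10% and 9% below are my assumptions.

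**1. The plan's own figure.** The critical value c is the largest number with P(X ≤ c | n = 184, p = 0.125) ≤ 0.05.
- P(X ≤ 15) = 0.0416 and P(X ≤ 16) = 0.0686, so c = 15, an observed 15/184 = 8.15%.
- In terms of the confidence bound, the one-sided 95% exact upper limit is 12.28% at 15 events (success) and 12.91% at 16 (failure).
- Power is P(X ≤ 15 | p = 0.0625) = 0.885, close to the stated 90%.

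The planned test does what it says against a fixed 12.5%.

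**2. Precision of the benchmark.** 0.125 × 216 = 27 events. The exact (Clopper-Pearson) 95% interval for 27/216 is 8.4% to 17.7%.

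**3. Chance of success if the device does nothing.** This is P(X ≤ 15 | n = 184, p), where p is the true rate without the device.

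| True rate without device | P(success), no device effect |
|---|---|
| 12.5% | 4.2% |
| 11% | 13.0% |
| 10% | 24.3% |
| 9% | 40.5% |

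All four rates lie inside the interval in step 2. At 10%, the chance is 24.3/4.2, or about 5.8 times the chance at 12.5%.

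**4. What the chart-review cases could add.** For 184 vs 150 with true rates of 6.25% vs 12.5%, power at one-sided 0.05 is 0.557 (Fisher exact) or 0.633 (score test). The expected risk difference is 6.25 percentage points. The approximate half-width of its 95% CI, without stratification, is 1.96 × √(0.0625 × 0.9375/184 + 0.125 × 0.875/150) = 0.063, or 6.3 points. The comparison is informative but cannot carry the decision.

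**5. Why direction alone is not enough.** Suppose both groups truly have 10%. The trial succeeds with probability 0.243. The probability that it succeeds and the 150 controls also show a higher rate is 0.207. So 0.207/0.243 = 85% of these false successes would still appear to be confirmed. The estimate and its interval are needed.

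**The case against.** A fixed performance goal is an accepted basis for a single-arm trial. The aim says in the same phrase that the comparison is with the historical rate, and the lack of a concurrent control is acknowledged. Supportive analyses are often left to an analysis plan, which is not shown here. The remark about overestimation sits among the cost-model inputs and is not expressly about the 12.5%; applying it there is an inference, though a reasonable one. All of this stands. It is why the primary test should stay and why the point is an improvement to the plan and not an error in it. It does not remove the mismatch, because the aim, the success rule and the restriction of the sensitivity work to cost are all stated in the article.

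A reader might go further in several ways that the document does not support:
- *That the true type I error is about 9%.* A figure of that size comes from also treating 27/216 as a random sample. That is a two-sample question; the planned test against a fixed 12.5% has error 4.2%.
- *That the chart-review cases are unused for clinical outcomes.* The Health economics section does plan to compare outcomes. What is missing is a link to the primary conclusion.
- *That excluding anaemia and coagulopathy makes this a lower-risk population than the benchmark's.* The benchmark study's eligibility criteria are not given.
- *That the chart data will not be centrally adjudicated.* The article does not say either way.
- *That a separate tipping-point analysis is needed.* The reported upper bound already is the lowest benchmark that the result would beat.

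**Conclusion.** The point holds as a limit on interpretation. The primary test is valid for showing a rate below a fixed 12.5%, but success does not by itself show that the monitor reduced bleeding. With no device effect, the chance of success is 4.2% if the underlying rate is 12.5%, and 13%, 24% or 41% if it is 11%, 10% or 9%. Those lower rates are assumptions. They are compatible with the benchmark's own sampling error, but nothing in the article shows that they apply. The conclusion also rests on reading the overestimation remark as relevant to the 12.5%. The change is worth making because the control cases are already being collected and it affects only analysis and wording.

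**What to change.** Leave the primary test, the 12.5% threshold and the 184 evaluable subjects as they are. In Analysis of primary efficacy end points, make these changes:

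1. Add a prespecified supportive comparison of access-site BARC III or V bleeding between the trial's primary analysis population and the chart-review cases. Use the same event criteria in both groups, stratify by site, and report the risk difference with a 95% CI. State that it is not a success criterion.
2. Describe a primary success as *below a 12.5% performance goal*. Support any statement that the monitor reduced bleeding with the estimate and interval from item 1, not merely with the direction of the difference.

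**Cost.** No additional patients are needed, since the chart review is already planned. The work is applying the primary end-point definition to the chart data, one further analysis, and rewording. The drawbacks are retrospective chart data and power of only about 56% to 63% (one-sided 0.05) for 12.5% vs 6.25%, so an inconclusive interval is quite possible and should be reported as such.

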### Study procedure

The study is divided into 3 timepoints: preprocedure, day of procedure, and postprocedure. Figure 3 summarizes the study flowchart. During the preprocedure timepoint, the Impella endovascular access procedure will be planned, and an assessment of baseline signs and symptoms will be collected. On the day of the procedure, high-risk PCI with Impella will be performed in accordance with the institution’s standard practice. The Saranas EBBMS sheath will be inserted in the femoral vein, ipsilateral to the Impella device (Central Illustration). Briefly, the data to be collected are the type of coronary intervention under Impella support; type of Impella device; type of Impella sheath; Impella bore sheath size; type of vessel cannulated with the Saranas EBBMS (eg, femoral vein); access technique (eg, ultrasound-guided, micropuncture, anterior vs posterior puncture); investigator’s actions in response to any bleed detection, eg, anti-thrombotic reversal, termination of the procedure, additional imaging, or interventions; and recording of adverse events and/or device complications. If angiograms are performed before and after the large-bore arterial access, these will be sent to the imaging core laboratory for adjudication of any bleeding or safety events.

**Figure 3 fig3:**
[figure not shown]
**Study flowchart of the SAFE-MCS study.** The study is divided into 3 timepoints: preprocedure (green), day of procedure (yellow), and postprocedure (red). EBBMS, Early Bird Bleed Monitoring System; MCS, mechanical circulatory support; PCI, percutaneous coronary intervention.

**Central Illustration fig4:**
[figure not shown]
The SAFE-MCS study will enroll 184 patients undergoing complex PCI supported by Impella with the use of a Saranas Early Bird Bleed Monitoring System in the ipsilateral femoral vein. The primary endpoint is the in-hospital rate of access-site related bleeding BARC III or V**.** EBBMS, Early Bird Bleed Monitoring System; MCS, mechanical circulatory support; PCI, percutaneous coronary intervention; SAFE-MCS, Safe Surveillance of PCI Under Mechanical Circulatory Support with the Saranas Early Bird Bleed Monitoring System.

Either during the PCI procedure or after removal of the Impella and closure of the arterial entry site, the Saranas EBBMS will be activated and remain in the femoral vein to monitor for a minimum of 2 hours postprocedure. Once the device is removed and the subject is discharged, the device will be shipped for decontamination and assessment of the impedance response by the sponsor.

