**Figure 1 fig1:**
[figure not shown]
**The Early Bird Bleed Monitoring System from Saranas.** The system consists of a standard 6F or 8F endovascular access sheath with embedded electrodes and a user interface display, which houses a printed circuit board assembly running an algorithm that analyzes bioimpedance and can trigger visible and audible indicators to communicate the state of change in bioimpedance.

After Saranas EBBMS insertion and activation, baseline bioimpedance readings are collected, and the device detects changes in bioimpedance as a response to an active bleed (Figure 2). The user interface display features a 3-level bleed indicator system that sequentially illuminates light emitting diode (LED) indicators to show an increase in bleed progression at the following levels:•Level 1 indicator (first LED) is triggered by the early onset of a bleed. An audible alert is momentarily activated once this level is triggered.•Level 2 indicator (second LED) is triggered as the bleed progresses when a bioimpedance threshold is reached. An audible alert, longer in duration than the first LED, is momentarily activated once this level is triggered.•Level 3 indicator (third LED) is triggered as the bleed continues to progress further when a higher bioimpedance threshold is reached. An audible alert is activated once this level is triggered and requires the attending clinician to silence the device by pressing the silence button.

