**Figure 2 fig2:**
[figure not shown]
**The Early Bird Bleed Monitoring System and relationship between bioimpedance and bleed monitoring.** The Early Bird Bleed Monitoring System provides a bleed detection array via embedded electrodes, continuously monitoring and interrogating changes in regional bioimpedance. It has been demonstrated that there is a consistent correlation between a decrease in bioimpedance and an increase in extravascular fluid accumulation (bleeding).^12^

Prior work in an animal model has demonstrated the performance of the EBBMS (sensitivity and specificity of 100%) in detecting the onset of access-related bleeds as low as ∼50 mL (level 1) and to continuously assess its progression (level 2, ∼100 mL; level 3, ∼200 mL).^12^ A first-in-human study of patients (N = 60) undergoing a variety of elective endovascular procedures demonstrated the safety and accuracy of the EBBMS for the real-time detection and monitoring of access site-related bleeding events. The study demonstrated a high level of agreement between the EBBMS and postprocedural computed tomography to identify periprocedural bleeding events. Indeed, the EBBMS correctly identified bleeding status (bleed or no bleed) in all patients, which included 35% of patients with no bleed and 65% with a bleed, as confirmed by computed tomography. Importantly, among patients with EBBMS-reported bleeding, approximately one-third occurred during the procedure and approximately two-thirds occurred after the procedure.^13^

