## Design of the SAFE-MCS study

The Safe Surveillance of PCI Under Mechanical Circulatory Support with the Saranas Early Bird Bleed Monitoring System (SAFE-MCS; NCT05077657) is a multicenter, single-arm, open-label study to evaluate the safety of complex high-risk PCI using the Impella (Abiomed) in conjunction with the Saranas EBBMS. The study will enroll 184 evaluable subjects at up to 15 US centers. Evaluable subjects are defined as all participants who had an EBBMS placed ipsilateral to MCS and had postprocedural monitoring by the EBBMS for a minimum of 2 hours. The study is anticipated to be approximately 24 months in duration. The duration of each subject’s participation will be the duration of the index hospitalization. The study is funded by Saranas, Inc, with an independent clinical events adjudication committee (Cardiovascular Research Foundation) and an independent imaging core laboratory (Medical Metrics).

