### Study population

The complete inclusion and exclusion criteria are shown in Table 1. Briefly, patients who are ≥18 years of age who plan to undergo a complex and high-risk PCI requiring MCS with an Impella 2.5 or CP (Abiomed) via transfemoral arterial are eligible for the study. The Saranas EBBMS will be used in the ipsilateral femoral vein to monitor bleeding events during the periprocedural period. The study subject will be informed of the nature of the study, agree to its provisions, and provide written informed consent as approved by the institutional review board of the respective clinical site. Key exclusion criteria include absolute contraindications or allergy to iodinated contrast that cannot be adequately treated with premedication; active bleeding; incapacity to safely access the femoral artery or femoral vein; significant femoral, iliac, abdominal, or thoracic aortic disease that precludes placement of MCS; anemia (hemoglobin <9 g/dL), thrombocytopenia (platelet count <50,000 cells/mL), history of bleeding diathesis or coagulopathy, or hypercoagulable states; active infection not controlled with antibiotic therapy; current pregnancy or women of child-bearing potential without documented negative pregnancy test; estimated life expectancy <24 hours; and patient is in cardiogenic shock at the time of enrollment.

**Table 1 tbl1:** SAFE-MCS inclusion and exclusion criteria.

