### Analysis of secondary efficacy end points

The frequency and percentage of activation of each EBBMS indicator (none/level 1/level 2/level 3) and all BARC type III or V bleeding (no bleeding/type III/type V) will be assessed.

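### Because the EBBMS may be activated during PCI or only after closure, the pooled indicator table and the indicator-BARC association mix two monitoring windows

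*Protocol article*

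**What the plan says.** All references are to the protocol article.

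- **Start of monitoring** (Study procedure, text after the Central Illustration): "Either during the PCI procedure or after removal of the Impella and closure of the arterial entry site, the Saranas EBBMS will be activated". Nothing says which option applies to which subject.
- **Reference point** (The Saranas Early Bird Bleed Monitoring System): "After Saranas EBBMS insertion and activation, baseline bioimpedance readings are collected". The device then responds to changes in bioimpedance.
- **Stated purpose** (Study population): "The Saranas EBBMS will be used in the ipsilateral femoral vein to monitor bleeding events during the periprocedural period".
- **Evaluability** (Design of the SAFE-MCS study): besides ipsilateral placement, subjects count if they "had postprocedural monitoring by the EBBMS for a minimum of 2 hours". No monitoring during the procedure is required.
- **Analysis** (Analysis of secondary efficacy end points): "The frequency and percentage of activation of each EBBMS indicator (none/level 1/level 2/level 3") is to be assessed, with no split by activation time. Under Sample size calculations and assumptions, a secondary aim is to relate indicator level to BARC type.
- **Earlier human data** (The Saranas Early Bird Bleed Monitoring System, N = 60): all patients were correctly classified, "which included 35% of patients with no bleed and 65% with a bleed". Among those with EBBMS-reported bleeding, "approximately one-third occurred during the procedure and approximately two-thirds occurred after the procedure".

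**The concern.** An indicator level measures change since baseline, and the baseline moves with activation. A subject activated during PCI is observed from some point in the procedure onward. A subject activated after closure is observed only for new bleeding from then on. One table of none, level 1, level 2 and level 3 adds these together, so its value depends partly on when operators switch the device on.

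The association with BARC type is the analysis most exposed. BARC events are adjudicated over the hospital stay, whereas an indicator can exist only after activation. A BARC III bleed during the procedure in a late-activated subject may be cross-tabulated against 'none' because the device was off. In the table this looks the same as a bleed that the device was monitoring and failed to detect.

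**Working it through.** **1. The article's own figure, and whether it is touched.** The article gives no expected value for the indicator incidences. Its only computed figure is the sample size: 184 evaluable subjects, 12.5% against 6.25%, exact one-sample binomial test, one-sided alpha 0.05, 90% power. With at most 15 bleeds in 184 counted as success, the exact alpha is 0.0416 and the exact power 88.5%, close to the stated 90%. Activation time enters none of these inputs. The endpoint is adjudicated bleeding, counted whether or not the device was on.

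**2. Inputs for the indicator incidence.**

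- Share of patients with a bleed: 65% (first-in-human study).
- Share of EBBMS-reported bleeding that arose during the procedure: about 1/3 (same study).
- Share of subjects activated after closure: f. The article does not give it, so a range is shown.
- Assumptions: each bleeder has one onset; bleeds that begin before a late activation have stopped by then and trigger nothing; subjects activated during PCI lose nothing. The second makes the loss in the late group a worst case.

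**3. Formula.** Observed any-level incidence = true incidence × (1 − f/3). Subjects missed = 184 × true incidence × f/3.

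| f | True 65% | Missed of 184 | True 30% (assumed) | True 20% (assumed) |
|---|---|---|---|---|
| 0.25 | 59.6% | 10 | 27.5% | 18.3% |
| 0.5 | 54.2% | 20 | 25.0% | 16.7% |
| 0.75 | 48.8% | 30 | 22.5% | 15.0% |
| 1 | 43.3% | 40 | 20.0% | 13.3% |

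For example, at f = 0.5: 0.65 × (1 − 0.5/3) = 0.542, and 184 × 0.65 × 0.5/3 = 19.9. The relative loss is f/3, so it cannot exceed one third under these assumptions.

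**4. Direction, level by level.** The article gives approximate volumes from an animal model: 50 mL for level 1, 100 mL for level 2, 200 mL for level 3. Take an illustrative bleed of 150 mL before a late baseline and 60 mL after it. The total is 150 + 60 = 210 mL, in the level 3 range, but the change since baseline is 60 mL, in the level 1 range. The subject drops out of 'level 2 or higher' and 'level 3', so those incidences fall. If the table counts each subject once at the highest level, the level 1 count rises by one.

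**The case against.** **The endpoint is activation of an indicator, not bleeding.** A subject whose indicators never lit is correctly counted as 'none', and as a description of the device in routine use the count is not biased. This stands, and it is why the bias is stated only for the figures read as measures of periprocedural bleeding. It does not rescue the association with BARC type, which compares the indicator with bleeding itself over unequal windows.

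**Periprocedural normally includes the time just after a procedure.** This also stands: the two statements are not a flat contradiction. But the article does not say which part of the period the indicator endpoint covers, and its two activation options give different answers.

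**An article leaves detail to the full protocol.** The list of collected data is introduced as brief, and the flowchart is not shown, so the absence of an activation time there does not prove that none is recorded. That is accepted. The point rests on what the article does state: two start times and one unsplit analysis.

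**The size is speculative.** The 65% and one-third come from 60 mixed elective endovascular cases, not Impella-supported PCI, f is unknown, and a bleed that continues past activation can still trigger an indicator. All of this stands. The table gives a range, not a prediction.

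**Stronger readings that the article does not support.**

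- A reader might infer that late activation places the baseline after the whole period of bleeding risk. By the article's own account, about two-thirds of EBBMS-reported bleeding came after the procedure, and late activation can still capture part of that.
- A reader might infer that each of the three level incidences is biased low. Step 4 of the working shows that an exclusive level 1 count could rise.
- A reader might infer that the primary result is compromised. Ascertainment of the primary endpoint does not depend on activation. Splitting the primary rate by activation timing would add little: 184 × 0.0625 = 11.5 expected events.

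**Conclusion.** The concern holds for the secondary indicator endpoint and the indicator-BARC association. Activation time is left open, the baseline follows it, and the analysis pools both kinds of subject. As measures of periprocedural bleeding, the any-level incidence and the incidences at or above each level are biased low. A bleed before activation can be misread as a device miss.

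The relative loss in any-level incidence is f/3, from nothing if no subject is activated late to one third if all are. This rests on carrying over the first-in-human split and on earlier bleeds having stopped by activation. The direction for an exclusive level 1 or level 2 count is not determined. The primary endpoint, its success rule and N = 184 stay as they are. The change is worth making, but the primary test does not depend on it.

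**What to change.** - Record the time of EBBMS activation relative to large-bore arterial access and to closure.
- Report indicator incidence separately for subjects activated before and after closure, and label the second group as post-closure monitoring only. State whether the level categories are exclusive or cumulative.
- In the indicator-BARC association, count only BARC events with onset after activation, or show earlier events in a separate 'before baseline' category instead of against 'none'.
- Reconcile the two activation options in Study procedure with the periprocedural monitoring described in Study population. Which activation time should apply is for the investigators and sponsor; no rule is proposed here.

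The cost is one time field on the case report form, if it is not already there, some analysis wording, and smaller groups for each indicator estimate. The groups will not be randomised, so differences between them should be described, not attributed to activation timing.
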